## Abstract

**Background:**

A central tenet in developmental psychopathology is that childhood rearing experiences have a major impact on children’s development. Recently, candidate genes have been identified that may cause children to be differentially susceptible to these experiences (i.e., susceptibility genes). However, our understanding of the differential impact of parenting is limited at best. Specifically, more experimental research is needed. The ORCHIDS study will investigate gene-(gene-)environment interactions to obtain more insight into a) moderating effects of polymorphisms on the link between parenting and child behavior, and b) behavioral mechanisms that underlie these gene-(gene-)environment interactions in an experimental design.

**Methods/Design:**

The ORCHIDS study is a randomized controlled trial, in which the environment will be manipulated with an intervention (i.e., Incredible Years parent training). In a screening, families with children aged 4–8 who show mild to (sub)clinical behavior problems will be targeted through community records via two Dutch regional healthcare organizations. Assessments in both the intervention and control condition will be conducted at baseline (i.e., pretest), after 6 months (i.e., posttest), and after 10 months (i.e., follow-up).

**Discussion:**

This study protocol describes the design of a randomized controlled trial that investigates gene-(gene-)environment interactions in the development of child behavior. Two hypotheses will be tested. First, we expect that children in the intervention condition who carry one or more susceptibility genes will show significantly lower levels of problem behavior and higher levels of prosocial behavior after their parent(s) received the Incredible Years training, compared to children without these genes, or children in the control group. Second, we expect that children carrying one or more susceptibility genes will show a heightened sensitivity to changes in parenting behaviors, and will manifest higher emotional synchronization in dyadic interchanges with their parents. This may lead to either more prosocial behavior or antisocial behavior depending on their parents’ behavior.

**Trial registration:**

Dutch Trial Register (NTR3594)

## Background

A central tenet in developmental psychopathology is that childhood rearing experiences have a major impact on children’s development across life
[1]. At the same time, we know that not all children are equally susceptible to these experiences
[2]. Grounded in a diathesis-stress model, there has been growing attention for research on individuals’ genetic susceptibility to parenting. The diathesis-stress model holds that some children, due to a specific vulnerability, are more likely to be negatively affected by environmental risk, such as with parental harshness, than others
[3-5].

A typical characteristic of these studies is that they only examined environmental adversity and negative child outcomes. It may therefore be that we, for a long time, only studied so-called *dandelions*; the resilient children that do well even in the face of severe adversity
[6]. In doing so, we may have overlooked the *orchids*; children who will suffer severely if ignored or maltreated, but flourish spectacularly when receiving adequate care. This metaphor forms the basis of an intriguing alternative hypothesis, namely the differential susceptibility hypothesis which holds that some children, due to a specific susceptibility factor, are more likely to be affected by environmental factors, *for better and for worse*[7,8].

Preliminary evidence for this differential susceptibility hypothesis has accumulated over the past years. Previous studies demonstrated, for example, that children with the dopamine receptor D4 (DRD4) 7-repeat allele showed significantly more externalizing problem behavior when mothers were insensitive, but also showed less problem behavior when mothers were highly sensitive, compared to those without the DRD4 7-repeat allele
[9]. Studies have identified several candidate genes underlying children’s differential susceptibility (e.g., monoamine oxidase A (MAOA) gene; dopamine transporter (DAT1) gene, dopamine receptor D4 (DRD4) gene, dopamine receptor D2 (DRD2) gene, serotonin-transporter (5-HTTLP-R) gene, and the catechol-o-methyltransferase (COMT) gene
[10-15].

However, the tenability of the genetic differential susceptibility hypothesis is still unclear, for several reasons. First, most previous studies only measured the presence or absence of environmental adversity and developmental problems, but not environmental enrichment and children’s competence. The absence of parental maltreatment, however, is not the same as parental warmth or sensitivity
[16]. Only environmental conditions and outcomes ranging from dysfunction to competence make it possible to avoid ceiling effects in testing differential susceptibility
[7,17,18]. Most importantly, most previous studies used correlational designs
[19] and therefore alternative explanations for gene-environment (G × E) interactions cannot be ruled out. For example, children with oppositional behavior may be, genetically, more likely to evoke harsh parental discipline and to actively select environments that support their problem behavior.

Trials in which families are randomly distributed across different environmental conditions offer a solution to this problem
[20,21], because they permit a manipulation of the environment that is *independent* of children’s genetic makeup and developmental histories. To our knowledge four randomized controlled trials on G × E interactions in children’s social emotional development have been conducted so far
[17,22-24].

These pioneering studies delivered important new insights, however their impact suffered from limitations as well. First, although the trials measured environmental enrichment the outcome was usually measured as a decrease in adolescent and child problem behavior, overlooking a possible increase in competent behavior. However, as argued above, to adequately examine differential susceptibility measurements of both environment and child behavior should range from dysfunction to competence. Second, the trials did not examine the possible underlying behavioral mechanism through which a G × E interaction may lead to different behavioral outcomes. It may be that carriers of candidate susceptibility genes show heightened behavioral reactivity. For example, children with low levels of dopaminergic functioning, associated with low reward sensitivity
[25], may improve more during and after parent management training than those with high levels of dopaminergic functioning associated with high reward sensitivity, because they can benefit more from the individualization of use of rewards and extensive praising by parents. Likewise, children with decreased serotonergic functioning
[25], associated with negative affect/mood, may improve strongly during and after parenting training due to the effect of an increase in positive parental emotions on this affect/mood. A highly reactive child will likely show an intense, mirroring emotional response to both negative and positive discipline
[27,28], which, in turn may lead to emotional synchronization in parent–child interactions. This congruency in affect may then lead to the development of either problem or prosocial behavior, depending on either positive or negative interactions with parents. Therefore, research should also investigate genetic expression “outside the skin”: the mechanisms through which genetic variation moderates the impact of environmental influences on individuals’ development. A randomized controlled trial can test hypotheses about underlying behavioral processes by examining whether certain mechanisms change in the experimental condition, mediating the intervention effect
[29].

### Aim and hypotheses

The ORCHIDS study is a genetically informed randomized controlled trial to examine possible G × E and G × G × E (i.e., polygenetic) interactions in the development of child behavior. The study examines parenting in its full scope, from both harsh and inconsistent to positive, sensitive, and appropriate parenting behavior as well as from children’s problem behavior and difficulties to their skills, competencies, and strengths. The primary aim is to investigate whether enrichment of the environment, based on the Incredible Years (IY) parent training, has more effect on a genetically susceptible subgroup of children, and to investigate why this may be the case. We expect that the parent training will bring about an environmental enrichment, leading to behavior changes in the participating parents. Two hypotheses will be tested. First, we expect differential susceptibility, which means that children in the intervention condition who carry one or more susceptibility genes (i.e., carrying a MAOA low activity (short) allele; DAT 10-repeat allele; DRD4 7-repeat allele; DRD2 A1 allele; 5-HTTLPR short allele; and or a COMT val allele) will show a significantly higher decrease of problem behavior and increase of prosocial behavior after their parent(s) received the parent training, compared to children without such susceptibility genes and children in the control group. In the control group, we expect this same genetic subgroup to show most behavior problems and least prosocial behavior. Second, we expect that emotional synchronization in parent–child interactions will mediate the intervention effect. Specifically, we expect that children who carry one or more susceptibility genes show a higher synchronization to their parents’ affect than children without these susceptibility genes. Therefore, we expect these children to benefit most from the increase in parental positive affect and sensitivity induced by the Incredible Years intervention.

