## Methods/Design

### Design

The ORCHIDS study is a randomized controlled trial with an intervention (i.e., the Incredible Years parent training) and a control condition that tests gene-based differential susceptibility to changes in parenting. Participants will be 480 families, with children aged 4–8 who show mild to (sub)clinical externalizing behavior problems. Of those families, 160 will be randomly assigned to the intervention condition and 320 families to the control condition. After enrollment in the trial and randomization, the baseline assessment (pretest) will be carried out. The Incredible Years (IY) program will be implemented after these baseline assessments. Participants in the control condition will receive no intervention, but are allowed –and, in case needed, are assisted– to seek mental health care and parenting support through regular services. Posttest and follow-up assessments will be conducted after 6 months and after 10 months, respectively. Approval for data collection was obtained from the central committee on research involving human subjects in The Netherlands (METC UMC Utrecht, protocol number 11-320/K).

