### Analyses

First, using independent *t*-tests, we will examine whether randomization was successful, comparing baseline levels of externalizing and prosocial behavior across the intervention and control condition. Possible significant differences at baseline will be used as covariates in analyses
[44]. Second, as the longitudinal data of individuals will be nested in families, multilevel latent growth curve analyses in Mplus
[45] will be performed. In this analysis, we will test the interaction between the variables ‘group’ (i.e., intervention vs. control) and ‘genotype’ (i.e., susceptible genotype vs. non-susceptible genotype) to examine possible G × E interactions. In addition, we will take into account families’ ethnic background (i.e., Caucasian vs. non-Caucasian) and additional parental support or (mental) health care families received during the study (i.e., additional self sought care vs. no additional self sought care). Ethnic background and additional care will both be used as covariates in the analyses.

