## Discussion

The ORCHIDS study described in this protocol is a genetically informed randomized controlled trial targeting families with children aged 4–8 who show mild to (sub)clinical behavior problems. The primary aim of ORCHIDS is to assess possible G × (G×)E interactions in the development of child behavior in its full scope – that is, from children’s problem behavior to their competencies. Our large scale randomized controlled trial is one of the first experimental studies of G × E interactions in social development. Experimental manipulation of the environment is crucial in understanding G × E interactions, because it is the only way to prevent confounding gene-environment covariation.

Additional to a single gene approach, we will investigate possible cumulative effects of multiple candidate genes (i.e., G × G × E or polygenetic interactions
[46]). Also, we will make a first attempt to obtain more insight into the behavioral mechanism underlying these G × E interactions by examining (changes in) emotional synchronization in observed parent–child interactions.

Better insight into individual differences in, for example, reactivity to positive parenting behavior like praise, associated with dopaminergic and serotonergic functioning, may help improve the tailoring of behavioral parent training. This seems necessary as the mean effect size of these interventions is modest (Cohen’s *d* = 0.47
[47]). Individualization of use of rewards and praise may help increase the efficiency of these parenting skills. For example, if the emotional significance of the positive message of praise is less well processed, associated with altered dopaminergic functioning, both verbal and nonverbal enthusiasm may be particularly relevant for this specific subgroup of children
[26]. Thus, instead of delivering interventions in a standardized way, parenting programs may benefit from an individualized approach based on insights from results of studies like the present one.

Despite the strengths and innovative aspects of ORCHIDS, there are some issues that our study is unable to take into account. Differential susceptibility to parenting may also be caused by environmental influences that alter the effects of genes (i.e., epigenetics), rather than by specific DNA sequences or a certain number of repeats alone
[48]. Human development is an active process powered by a continuous interaction between the genome and the environment

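### One carrier rule for X-linked MAOA in boys and girls, with no sex term in the model, partly ties the MAOA genotype group to sex and leaves heterozygous girls without a class of their own

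*Protocol article*

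**What the plan says.** The Aim and hypotheses section of the protocol article predicts a larger response in "children in the intervention condition who carry one or more susceptibility genes". It names one allele for each of six genes, and MAOA appears in that list in the same carrier form as the rest: "carrying a MAOA low activity (short) allele; DAT 10-repeat allele". Neither sex nor number of copies is mentioned.

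The Analyses section tests group by genotype, with genotype in two classes: "susceptible genotype vs. non-susceptible genotype". On adjustment it states: "Ethnic background and additional care will both be used as covariates in the analyses". Further covariates can enter only through a baseline check limited to "comparing baseline levels of externalizing and prosocial behavior across the intervention and control condition".

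The Discussion section confirms that genes are tested one at a time as well as together: "Additional to a single gene approach, we will investigate possible cumulative effects of multiple candidate genes". The Design section says: "Participants will be 480 families, with children aged 4–8", with no restriction by sex. Child sex is mentioned nowhere in the article. Under Outcomes, moderation by genotype is the primary outcome, so the MAOA test belongs to the primary analysis.

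**The concern.** MAOA lies on the X chromosome. A boy has one copy and is either low or high activity. A girl has two, and in a heterozygous girl X-inactivation means that genotype alone does not fix activity. A rule of carrying at least one low-activity allele, applied alike to both sexes, has two consequences:

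- Girls enter the susceptible group more often than boys, so a comparison of MAOA groups is partly a comparison of sexes.
- Heterozygous girls are pooled with hemizygous low-activity boys and homozygous low-activity girls, although their activity class is unknown.

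If the response to the parent training differs between boys and girls, part of that difference would be reported as a gene-by-environment effect. Randomization does not prevent this. It makes treatment independent of both genotype and sex, but it does not separate the two as moderators. The planned baseline check would not reveal the problem either, since it compares behavior scores between arms and not sex between genotype groups.

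**Working it through.** The article states no figure on this point, so there is nothing to reproduce.

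**Inputs from the article:** 480 families, 160 intervention and 320 control (Design); a training effect of d = 0.20 (Sample size calculation); the carrier rule (Aim and hypotheses); two genotype classes (Analyses).

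**Assumptions, not in the article:** low-activity allele frequency q = 0.30 to 0.40; girls' share g = 35% to 50%; Hardy-Weinberg proportions; one child per family.

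**Step 1, carriers by sex.** Boys: q. Girls: 1 − (1 − q)². At q = 0.30 this is 30% against 51%; at q = 0.40, 40% against 64%. The two differ for every q between 0 and 1.

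**Step 2, heterozygous girls.** Their share of all girls is 2q(1 − q): 42% at q = 0.30 and 48% at q = 0.40. Their share of carrier girls is 2(1 − q)/(2 − q): 82% and 75%. This exceeds one half only if q < 2/3.

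**Step 3, sex mix of the two groups.** Take q = 0.40 and g = 40%. Carriers are 0.60 × 0.40 = 0.240 (boys) plus 0.40 × 0.64 = 0.256 (girls), total 0.496. Girls are 0.256/0.496 = 51.6% of carriers. Non-carriers are 0.360 boys and 0.144 girls, so girls are 0.144/0.504 = 28.6%. The gap is 0.230. At the corners of the assumed range:

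| q | girls in sample | girls among carriers | girls among non-carriers | gap | heterozygous girls of 480 |
|---|---|---|---|---|---|
| 0.30 | 35% | 48% | 27% | 0.20 | 71 |
| 0.30 | 50% | 63% | 41% | 0.22 | 101 |
| 0.40 | 35% | 46% | 24% | 0.22 | 81 |
| 0.40 | 50% | 62% | 38% | 0.24 | 115 |

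**Step 4, leak into the interaction.** Let δ be the difference in training effect between girls and boys. With no true MAOA effect, the effect in each MAOA group is the boys' effect plus δ × (share of girls). The apparent MAOA × group effect is then δ × gap, or 0.20δ to 0.24δ. Over a wider range (q = 0.20 to 0.60, 50% to 70% boys) it is 0.18δ to 0.30δ.

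**Step 5, size against the noise.** Suppose δ = 0.20 SD, as large as the whole training effect assumed in the sample size section. The spurious interaction is 0.04 to 0.05 SD. With carrier share C, the standard error of a simple post-score interaction contrast is 1/√[480 × (1/3) × (2/3) × C(1 − C)]. At C = 0.496 this is 1/√(106.67 × 0.250) = 0.194 SD; over the assumed range it is 0.19 to 0.20. The bias is thus 0.20 to 0.25 of one standard error, and a two-sided 5% test would reject about 5.5% to 5.7% of the time. If baseline adjustment shrinks the standard error (assumed correlation 0.7, factor √(1 − 0.49) = 0.714), the figure is about 5.9% to 6.4%.

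**Step 6, does excluding heterozygous girls cure it?** The low-activity share among the remaining girls is q²/[q² + (1 − q)²]: 0.09/0.58 = 16% at q = 0.30 and 0.16/0.52 = 31% at q = 0.40, against 30% and 40% in boys. The imbalance changes direction but does not go away.

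**The case against.** The strongest reply is that the allele list sits in a hypothesis statement, while the Analyses section says only "susceptible genotype vs. non-susceptible genotype" and does not spell out the grouping gene by gene. A fuller protocol or analysis plan may code MAOA by sex, and the covariate list is not declared complete. This carries some weight: silence about sex alone would be no finding in a condensed article. But the article does state a carrier rule for children of both sexes, two genotype classes and named covariates. Following that text produces the association shown above, and sex-specific coding would be a change to the stated rule.

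The second reply, that the harm is conditional and small, stands. The article gives no evidence that the training works differently in boys and girls. Even a sex difference equal to the whole assumed effect shifts the MAOA estimate by only about a quarter of a standard error. The other five genes are not touched, and in a cumulative score MAOA is one component of several.

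A reader might infer more than this, and the article does not support it:

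- That MAOA and sex are fully confounded. The association is partial (correlation about 0.20 to 0.24 under the assumptions used) and sex terms can separate the two.
- That most susceptible girls are necessarily heterozygous. This needs q < 2/3, and no allele frequency is given.
- That heterozygous girls certainly dilute a true effect. Their activity is undetermined, so dilution is possible but not shown.

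**Conclusion.** The point holds in limited form. As written, the MAOA rule makes genotype group partly associated with sex at any allele frequency, and it assigns heterozygous girls a class that their genotype does not establish. Under q = 0.30 to 0.40 and 35% to 50% girls, 0.20 to 0.24 of any sex difference in the training effect would pass into the MAOA × group estimate, and about 71 to 115 of the 480 children would be heterozygous girls. Bias follows only if the training effect differs by sex. It is then modest against sampling error and confined to the MAOA test and scores that include MAOA. It is still worth correcting, because the article justifies the randomized design as a way to exclude rival explanations of gene-by-environment effects, and this coding admits one that is easily removed.

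**What to change.** Add child sex and sex × group, on the same growth parameters as genotype × group, to the MAOA model and to any cumulative-score model that includes MAOA. These terms remove the leak; a sex main effect alone would not.

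Replace the single MAOA carrier rule with sex-specific coding: low or high in boys; low/low, high/high or heterozygous in girls, with heterozygous girls kept as their own class. Add a sensitivity analysis that excludes them, or analyse boys and girls separately. Use the same coding in the cumulative score.

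The cost is plan wording, a few model terms and some precision for MAOA. The sex terms alone widen the standard error by about 1/√(1 − 0.20²) to 1/√(1 − 0.24²), that is 2% to 3%. The separate class costs more, because heterozygous girls (15% to 24% of children under these assumptions) no longer inform the low-versus-high contrast. At q = 0.40 and 40% girls, C(1 − C) = 0.250 is replaced by 0.60 × 0.24 + 0.40 × 0.52 × 0.308 × 0.692 = 0.188, so the standard error rises from 0.194 to 0.223 SD. No new assessment should be needed: Table 1 lists genotyping and demographic characteristics at pretest, although it does not name sex, so its collection should be confirmed.

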## Methods/Design

### Design

The ORCHIDS study is a randomized controlled trial with an intervention (i.e., the Incredible Years parent training) and a control condition that tests gene-based differential susceptibility to changes in parenting. Participants will be 480 families, with children aged 4–8 who show mild to (sub)clinical externalizing behavior problems. Of those families, 160 will be randomly assigned to the intervention condition and 320 families to the control condition. After enrollment in the trial and randomization, the baseline assessment (pretest) will be carried out. The Incredible Years (IY) program will be implemented after these baseline assessments. Participants in the control condition will receive no intervention, but are allowed –and, in case needed, are assisted– to seek mental health care and parenting support through regular services. Posttest and follow-up assessments will be conducted after 6 months and after 10 months, respectively. Approval for data collection was obtained from the central committee on research involving human subjects in The Netherlands (METC UMC Utrecht, protocol number 11-320/K).

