### Randomization

Participants will be informed of the design of the study and will give consent prior to randomization. Randomization will occur through random selection of a participant number that is linked to either the intervention or control condition.

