### Data collection

An overview of all measurement occasions is given in Table
1. Both the recruitment, as well as the waves of data collection will be conducted in two separate cohorts in 2012/2013 and 2013/2014. The recruitment (i.e., screening) will take place in September-October 2012 and 2013. The pretests will take place in November-January 2012 and 2013. Families will be asked to fill in questionnaires in the presence of a researcher or research assistant during home visits. Furthermore, parent–child interactions will be videotaped during structured play situations. This procedure will be repeated twice after the pretest, namely at posttest and follow-up. Saliva samples for genotyping will be collected once during pretest.

**Table 1 T1:** Overview of measurements

**Measurement**	**Screening**	**Pre test**	**Post test (6 months after baseline)**	**Follow up (10 months after baseline)**
Demographic characteristics		*		
Child behavior:				
External behavior (ECBI)	*	*	*	*
Prosocial behavior (MESSY)		*	*	*
Temperament: (CBQ)		*	*	*
Strengths and Difficulties (SDQ)		*	*	*
Genotyping *(DRD4, DRD2, DAT1, COMT, 5-HTTLPR, MAOA)*		*		
Parenting behavior:				
PPI		*	*	*
Parent-child interaction:				
DPICS-R		*	*	*

*Note*. *ECBI* Eyberg Child Behavior Inventory, *MESSY* The Matson Evaluation of Social Skills with Youngsters, *CBQ* Children’s Behavior Questionnaire, *SDQ* Strengths and Difficulties Questionnaire, *DRD4* dopamine receptor D4 gene, *DRD2* dopamine receptor D2, *DAT1* dopamine transporter gene, *COMT* catechol-o-methyltransferase gene = *5-HTTLPR* = serotonin-transporter gene, *MAOA* monoamine oxidase A gene, *PPI* Parenting Practices Interview, *DPICS-R* Dyadic Parent-Child Interactive Coding System-Revised.

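### Families are randomised before the pretest and the only saliva sample, so parent-rated baselines may reflect knowledge of the arm, and families lost in between cannot enter the G × E analyses

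*Protocol article*

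**What the plan says.** The Design section of the protocol article gives the sequence as enrolment and randomisation, then pretest, then training: "After enrollment in the trial and randomization, the baseline assessment (pretest) will be carried out", followed by "The Incredible Years (IY) program will be implemented after these baseline assessments".

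The Randomization section adds that "Participants will be informed of the design of the study and will give consent prior to randomization" and that "Randomization will occur through random selection of a participant number that is linked to either the intervention or control condition". It does not say when the family or the home visitor learns the arm.

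Under Data collection, the pretest is a home visit: "Families will be asked to fill in questionnaires in the presence of a researcher or research assistant during home visits". Parent–child interaction is also filmed there, and "Saliva samples for genotyping will be collected once during pretest".

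Under Analyses, the pretest scores serve as a check: "we will examine whether randomization was successful, comparing baseline levels of externalizing and prosocial behavior across the intervention and control condition". Differences that reach significance become covariates. The main test is the interaction of group with genotype.

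One measure comes earlier. The Recruitment section sends the ECBI with the screening letter, and Table 1 marks it in the screening column. MESSY, DPICS-R and genotype first appear at pretest.

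**The concern.** A baseline is useful in a randomised trial because allocation cannot have affected it. Here it follows allocation. The two arms are also very different to live through: 14 to 16 weekly two-hour sessions, or no study intervention. A parent who knows the arm may rate the child differently at pretest, or may decline the visit.

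Two things are at stake. First, the first hypothesis compares behaviour change in trained families with that in control children, and a pretest score that moved because of allocation would enter that change. Second, DNA is sampled once, after randomisation. The genotyped sample can therefore be smaller than the randomised one, and it can differ from it in a way that depends on arm. The planned t-tests could not tell chance imbalance from allocation-driven reporting or loss.

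**Working it through.** **Order of events.** The Design section puts randomisation before the pretest, and Data collection puts saliva at the pretest. No section shown says that allocation is concealed from families or assessors until the visit is over. That the screening ECBI precedes randomisation follows from Recruitment, where it decides eligibility; Table 1 has no randomisation column.

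**Reporting shift.** Let *b* (in SD) be the difference between arms in pretest ratings that is caused by knowing the arm. The document gives no value.

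- Change from pretest: if the shift occurs at pretest only, the bias has size *b*. If the same shift recurs at every wave, it cancels.
- Linear slope over 0, 6 and 10 months (unweighted): the mean time is 5.333, the deviations are −5.333, 0.667 and 4.667, and their sum of squares is 50.667. The pretest weight is −5.333/50.667 = −0.105 per month, so a pretest-only shift moves the 10-month change by about 1.05*b*, in the direction opposite to the shift.
- Group × genotype: the bias is proportional to *b* in carriers minus *b* in non-carriers. It is zero if the shift is the same in both, which is plausible if parents do not know the genotype.

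**What the baseline t-test can detect.** With 160 and 320 families, the standard error of a baseline difference is √(1/160 + 1/320) = 0.097 SD. At two-sided α = .05, for assumed values of *b*:

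| Assumed *b* (SD) | Chance that the t-test is significant |
|---|---|
| 0 | 5% |
| 0.1 | 18% |
| 0.2 | 54% |

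A real shift in this range would often go unadjusted. When flagged, it would look the same as chance imbalance.

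**Loss before pretest.** The document gives no rate. Each 5% is 0.05 × 160 = 8 training families or 0.05 × 320 = 16 control families.

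For the effect on power, the plan gives no number for the interaction. As an illustration, take the ANOVA effect size at which 480 families give power of about .80 on 1 df with four groups, *f* ≈ 0.128. This value is back-solved and is not stated in the plan.

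| Assumed loss, both arms | Families genotyped | Power | Randomised to keep 480 |
|---|---|---|---|
| 5% | 456 | .78 | 506 |
| 10% | 432 | .76 | 534 |
| 15% | 408 | .73 | 565 |
| 20% | 384 | .71 | 600 |

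Loss that is equal across genotypes within an arm, and unrelated to response, leaves the interaction unbiased and costs only precision. Bias needs arm-dependent loss that is also related to genotype or to genotype-specific response.

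**The case against.** The strongest reply is that the reporting mechanism requires families to know their arm at the visit, and the article never says that they do. Drawing a number linked to an arm and disclosing it after the home visit would fit the text. Disclosure timing is also a detail that a condensed article may leave to the full protocol, and the study flow figure is not shown. This stands: the text supports *may know*, not *do know*.

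The primary outcome is moderation by genotype, which a uniform shift hardly touches. DPICS-R is observed rather than parent-rated, and training starts only after the pretest, so no treatment effect contaminates the baseline. These points stand too. They leave exposed the parent-rated training-versus-control comparisons, the randomisation check and the completeness of genotyping.

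A reader might infer that the bias could match the planned effect, by setting an assumed shift of 0.1 to 0.2 SD against *d* = .20. The document does not support that. The shift has no source and could be zero, it may persist and cancel, and .20 is the overall training effect, whereas the interaction is only called small.

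A reader might also infer that early withdrawers have no baseline at all. They do have a screening ECBI. It is a weaker covariate, though: selection at or above the 75th percentile restricts its range, it dates from September–October against November–January for the pretest, and it covers one outcome only.

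**Conclusion.** The point holds in a limited form. The order is stated outright: randomisation, then pretest, with the only saliva sample at that pretest. Parent-rated baseline ECBI and MESSY may therefore carry the effect of knowing the arm, and a family lost in between has neither pretest scores nor genotype. The training-versus-control comparisons in the first hypothesis and the baseline check are exposed to allocation-driven reporting and selective loss. The group × genotype contrast loses precision, and is biased only under the further condition on loss given above.

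The size of the shift and of the loss cannot be derived from the document. The 8 or 16 families per 5% are arithmetic on an assumed rate. The power figures rest in addition on a back-solved effect size, and the detection figures on an assumed shift. If allocation is in practice withheld until the pretest is complete, most of the concern falls away, but the text shown does not say so.

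**What to change.** For families not yet randomised, complete the whole pretest visit (questionnaires, video, saliva), then randomise and disclose the arm. Every randomised family that gave a usable sample then has a genotype. This looks feasible: recruitment is ongoing, a second cohort is planned, and training already starts after the pretest.

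If the order cannot change, withhold the arm from families and assessors until the pretest and saliva are done, and state this in the protocol. Losses before the visit could then not be driven by knowledge of the arm, although they would still reduce the genotyped sample.

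For families already randomised:

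- report losses between randomisation and pretest by arm;
- as a sensitivity analysis for the ECBI outcome only, adjust for the screening ECBI, and note its restricted range and earlier timing. It does nothing for MESSY, DPICS-R or genotype.

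The cost is a short amendment and slightly later forming of training groups. The procedure may also differ between cohorts, so adjust for cohort in the analysis.
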